## METHODS

2

### Setting and design

2.2

This study will be conducted in accordance with the National Health and Medical Research Council (NHMRC) guidelines and statements and will be performed at The University of Adelaide (SA, Australia). The trial was registered in the Australian New Zealand Clinical Trial Registry (ACTRN12622000642785p) and approved by the Human Research Ethics Committee of The University of Adelaide (HREC‐2022‐082). The study protocol complies with the SPIRIT 2013 recommendations (Standard Protocol Items: Recommendations for International Trials; Supplementary Table S1; Chan et al., 2013). Figure 1 depicts the overall schedule and time commitment for trial participants.

**FIGURE 1 eph13343-fig-0001:**
[figure not shown]
Schedule of enrolment, interventions and assessments. Abbreviations: CPM, conditioned pain modulation; EIH, exercise‐induced hypoalgesia; GPAQ, global physical activity questionnaire; NDI, neck disability index; PCS, pain catastrophizing scale; SF‐36, 36‐item short form survey; ‐t_1_, enrolment week 0; t_0_, allocation; t_1–2_, intervention, baseline and post‐intervention assessments; TS, temporal summation; TSK, Tampa scale of kinesiophobia.

This study is a randomized crossover trial, in which all participants will take part in all interventions, but the order in which they are assigned to the interventions is randomized. Participants will attend the first data collection session, during which baseline questionnaires and physical assessments will be measured, followed by the intervention, and a post‐intervention physical assessment will be measured. There will be a 1‐ to 2‐week washout period before the second data collection session, which is identical to the first session minus the baseline questionnaires, with a different intensity of intervention.

### Participants

2.3

The sample will consist of 80 adults, who will be enrolled into the study according to the following criteria. Inclusion criteria are as follows: Adults (19–65 years of age); and chronic NP (>12 weeks duration) with and without CS. Exclusion criteria are as follows: Known or suspected serious spinal pathology (e.g., metastatic, inflammatory or infective disease of the spine); confirmed fracture or dislocation at the time of injury; nerve root compromise (at least two of the following symptoms: weakness/reflex changes/sensory loss associated with the same spinal nerve); spinal surgery in the previous 12 months; history or presentation with psychosis, bipolar disorder, organic brain disorder or severe depression; individuals who are currently taking or have a history of taking anti‐depressant or anti‐convulsant medication; and answered ‘yes’ to any of the seven questions on the Physical Activity Readiness Questionnaire (PAR‐Q+) (Warburton et al., 2021).

Participants will be recruited through posters placed on the University campus and at supermarkets, and posts on social media. All potential participants will receive oral and written information, listing the participant's responsibilities, study risk and benefits, prior to prescreening and obtaining informed consent. Participants will be enrolled into the study after obtaining informed consent.

### Procedures

2.4

Participants who meet the inclusion criteria will be invited to attend two testing sessions: one to perform high‐intensity submaximal aerobic bicycle exercise (HIGH); and a second to complete a low‐intensity submaximal aerobic bicycle exercise (LOW). The order of these two testing sessions will be randomized. Participants will be asked to refrain from analgesics on the day of testing and to abstain from physically demanding activities, including exercise, for 48 h before testing. Participants will also be asked to abstain from nicotine, alcohol and caffeine for 12 h before testing.

Participants will be given a detailed explanation about the research study and the requirements of them. Informed consent will be obtained from the participants before collecting any data. Figure 2 depicts the flowchart of study procedure and the assessments conducted at each assessment time point. Participants will be randomized into two main groups, termed the INV‐A group and the INV‐B group, with INV‐A doing HIGH–LOW and INV‐B doing LOW–HIGH. Participants will wait 10 min before commencing the exercise intervention to prevent a carryover effect from the baseline physical assessments influencing exercise. During the waiting time, resting heart rate (HR) and blood pressure will be measured, and appropriate warnings and precautions will be briefed. Participants will then complete the assigned exercise intervention, immediately followed by postexercise assessment. The order of testing will be kept constant within each testing session, both before and after exercise. To prevent a carryover effect, the sessions will be scheduled 1–2 weeks apart.

**FIGURE 2 eph13343-fig-0002:**
[figure not shown]
Flowchart of study procedure and the associated assessment conducted.

### Randomization

2.5

The participants will be enrolled sequentially. After informed consent is obtained, participants will be allocated randomly to one of two groups: INV‐A or INV‐B. Block randomization will be performed with a 1:1 allocation ratio, using the website https://www.sealedenvelope.com/. A table with random numbers generated by the website will be used. Opaque and sealed envelopes containing cards with the name of the intervention group will be used to ensure concealed allocation. A researcher not part of the study will perform the allocation procedure. Owing to the nature of the study trial, blinding of the assessor and participants is not possible.

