### Data collection

2.6

Demographics, including age, sex, education level, duration of chronic NP, physical activity participation level (GPAQ; Cleland et al., 2014) and employment status, will be collected. The outcome assessments consist of questionnaires and central pain processing measurements. Questionnaires will be assessed at the start of each exercise session, and the central pain processing measurements will be performed twice at each session: at baseline; and postexercise.

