##### Primary outcome measures

###### Exercise‐induced hypoalgesia

Exercise‐induced hypoalgesia will be assessed through pain pressure threshold (PPT) measurement, followed by a fatigue‐inducing exercise stimulus, and lastly, the same PPT measurements. The PPT will be measured using Echo Wireless Algometer (JTECH Medical, UT, USA). The PPT will be measured at two sites; (1) over the C5/C6 spinous process in the cervical spine; and (2) over the muscle belly of the left tibialis anterior. To ensure accurate measurement, an ‘x’ will be marked on the testing site with a marker during baseline assessment, and the same site will be used for postexercise PPT assessment. Pressure will be applied on the testing site at a rate of ∼5 N/s. Participants will be asked to state verbally when the sensation changes from ‘comfortable’ pressure to ‘unpleasant’ pain sensation. Triplicate reading, with a 30 s interstimulus interval, will be taken at each site, and the mean values will be used for analysis. The PPT measurements will be taken before and after the fatigue‐inducing exercise stimulus. The fatigue‐inducing exercise stimulus will be an isometric wall‐squat. Participants will be asked to maintain a wall‐squat position until fatigue or for a maximum of 3 min.

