#### HIGH intervention

2.7.1

Participants will put on the Polar HR monitor chest strap (Polar H10; Polar Electro Oy, Kempele, Finland). The HR monitor will be connected to a bluetooth‐enabled device, which will display the HR. After measuring the resting HR and blood pressure, [La] will be measured. The rating of perceived exertion (RPE) scale will be explained to the participants. The RPE will be determined using Borg 6–20 point‐category scale (Williams, 2017). The participant's 75% of age‐predicted maximum HR [i.e., 0.75 × (220 − age in years)] will be calculated; this will be used as the target HR during exercise.

Participants will then go onto the stationary bicycle, with the seat height adjusted for optimal cycling posture. Participants will use the same bicycle, with the same adjustment made, on both sessions. After a quick instruction briefing to ensure safety, participants will then complete a standardized, submaximal bicycle aerobic exercise protocol, based on the aerobic power index (API) protocol. The API protocol has been found to be a safe and reliable submaximal exercise test for individuals with various clinical conditions (Furzer et al., 2012; Wallman et al., 2003), including chronic NP (Ickmans et al., 2017; Smith et al., 2017, 2020). The participants will start to cycle at 60–70 rpm at level 1 resistance, and the resistance will be increased by one or two levels every minute until attainment of the target HR. The increment of resistance level will be controlled by the researcher and will be based on the participant's HR response. The participants will then continue to cycle at this power output for 30 min. Heart rate and RPE will be recorded each minute during the increase in power output, then once every 3 min until the end of the exercise session.

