### Safety

5.2

All participants will be screened before enrolment using the PAR‐Q+ questionnaire to assess whether a participant is physically ready and safe to participate in the study. Stringent coronavirus disease 2019 precautions will be enforced according to university and government guidelines throughout the study. Baseline resting HR and blood pressure will be measured at each session, before exercise, to ensure the participant's safety. All data collection sessions will be supervised by an experienced exercise physiologist and overseen by a senior physiotherapy academic. All physical outcome measures and the exercise protocol have been found to be safe for the study population and have been used widely in various studies (Ickmans et al., 2017; Smith et al., 2017; Vaegter et al., 2016). A risk assessment and management plan has been developed with the University's Health, Safety and Wellbeing Team to eliminate or manage the likelihood and consequences of adverse events occurring. All adverse events will be assessed and managed in accordance with standard clinical practice at the study site and documented by the study team. All serious adverse events will be reported to the principal investigator and will be reported as required by the HREC approval process, and the appropriate steps will be taken, following the University's policy and guidelines. All adverse events will be recorded according to the registered data management plan.

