### Possible risks

5.3

There are potential risks to study participation. This is a randomized crossover trial investigating the effect of a single bout of two different aerobic exercise intensities on individuals with chronic NP. It is possible that the pain intensity and sensitivity might increase after exercise. With all exercise interventions there is increased risk of adverse events, such as cardiorespiratory events and musculoskeletal injuries. With prescreening conducted before the start of the intervention, the risks of adverse events are mitigated, and risks to participants are not anticipated to differ from ordinary risks of participating in any physical activities. Furthermore, the study has been developed carefully and designed pragmatically, with inclusion and exclusion criteria, to allow results to be as generalizable as possible without putting participants with severe conditions at risk, and a robust safety protocol will be in place. Participants with health conditions prohibiting them from performing exercise are excluded from the study. All potential participants will be given a ‘participant information sheet’ listing all study information, including potential risks, and all queries will also be answered before obtaining informed consent. All exercise sessions will be supervised by an experienced exercise physiologist and overseen by a senior physiotherapy academic.

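### Assessor blinding is ruled out for a reason that fits only the participants; observer bias in the pain tests could be reduced, though not eliminated, by simple masking

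*Protocol article*

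**What the plan says.** Section 2.5 (Randomization) describes concealed allocation by a researcher outside the study. It then states that "blinding of the assessor and participants is not possible", giving the nature of the trial as the only reason and nothing specific to the assessor.

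Other sections bear on whether that follows:

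- **Timing.** Section 2.6 says "the central pain processing measurements will be performed twice at each session: at baseline; and postexercise". Section 2.4 adds "Participants will wait 10 min before commencing the exercise intervention", and says that the bout is "immediately followed by postexercise assessment".
- **Who sets intensity.** Section 2.7.1: "The increment of resistance level will be controlled by the researcher". This researcher is not said to be the tester.
- **Who else attends.** Section 5.2: "All data collection sessions will be supervised by an experienced exercise physiologist and overseen by a senior physiotherapy academic". Section 5.3 repeats the supervision for the exercise sessions.
- **How outcomes are obtained.** For the pressure pain threshold (PPT), section 2.6.2 says "Pressure will be applied on the testing site at a rate of" about 5 N/s, and the endpoint is what the participant says. The same threshold is the test stimulus for conditioned pain modulation (CPM), during which staff encourage the participant to keep the hand in the ice bath. Temporal summation (TS) is a verbal rating after a pinprick train.

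The Discussion names one limitation, which concerns the single bout. It does not mention unblinded assessment.

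**The concern.** The sentence treats participants and assessor alike, although the reason given reaches only the first. A tester who knows that the participant has just done HIGH, and who expects more hypoalgesia from it, can ramp the algometer slightly differently or encourage more warmly. Such a shift depends on intensity, so it enters the HIGH–LOW contrast directly. The crossover removes stable differences between people but does not remove this.

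The exposure is uneven. It is greatest for the PPT ramp, which feeds both exercise-induced hypoalgesia (EIH) and CPM. It is smaller for ice-bath encouragement, which acts first on how long the hand stays in. It is limited for TS, where the stimulus force, count and frequency are fixed.

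**Working it through.** **1. Does the reason reach the tester?**

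- Intensity is set and seen during cycling, through resistance and target heart rate: 75% of age-predicted maximum for HIGH and 50% for LOW (sections 2.7.1 and 2.7.2).
- The pain tests are done before and after cycling (sections 2.4 and 2.6). No test described in section 2.6.2 needs resistance or target heart rate.
- At baseline the participant has not yet cycled, so there is no exertion cue. Nothing in the article prevents masking the tester to that session's intensity.
- After exercise the tests follow at once, so visible exertion and any lactate reading are cues. Masking is possible but partial.

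The stated reason therefore does not establish that the assessor cannot be blinded.

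**2. The plan's own sample size, as the source of 64.** From section 2.8: means 25.0 and 42.1 (difference 17.1), SDs 19.7 and 27.2, two-sided α = 0.05, power 0.80.

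- Pooled SD = √((19.7² + 27.2²)/2) = 23.75, so d = 17.1/23.75 = 0.72.
- The noncentral t calculation gives 31.27 per group, rounded up to 32, or 64 in total. Then 64/0.80 = 80.

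Both stated figures reproduce, and this point changes neither.

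**3. What a small systematic shift would do.** The documents give no size for observer bias, so the shift b, in SDs of the within-person HIGH–LOW difference, is assumed. Assume also no true effect, 64 completers and no multiplicity adjustment.

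Section 2.9 compares within-person differences between the two sequences with an unpaired t-test. With 32 per sequence, the bias adds +b in one sequence and −b in the other. The shift in the test statistic is 2b/√(2/32) = 8b, the same as b√64. Hence:

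false-positive rate = P(|Z + 8b| > 1.96)

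| b (assumed) | 8b | Rate |
|---|---|---|
| 0 | 0 | 5% |
| 0.1 | 0.8 | 12.6% |
| 0.2 | 1.6 | 36.0% |

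**4. Sensitivity to the assumptions.**

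- *Bias as a share of the planned 17.1.* Shifts of 10%, 20% and 30% are 1.7, 3.4 and 5.1 units. In a within-person comparison of 64 people, using the SDs of section 2.8 and an assumed correlation of 0.3 to 0.7, the rates are 8–11%, 16–29% and 30–56%. If the data are treated as two independent groups of 32, they are about 6%, 9% and 14%.
- *Multiplicity.* Section 2.9 plans a Bonferroni correction. If it covers three measures (assumption), the critical value is about 2.39. The rates for b = 0.1 and 0.2 become about 6% and 21%, against 1.7% without bias.

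**The case against.** The strongest reply is that masking would be weakest where it matters most. The tester meets someone who has just finished 30 minutes of cycling, then runs a wall-squat to fatigue, with lactate in the same assessment flow. The same participants return one to two weeks later for the other intensity, so a tester who guesses the first session knows the second, including at its baseline. Participants stay unblinded, and every primary endpoint includes their verbal report. All of this stands. A reader might infer that observer bias could be avoided altogether; the documents support only that it could be reduced.

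A reader might also infer that the plan has no protection left. That is not so. Allocation is concealed, test order is constant, sites are marked, the ramp rate is stated, PPT for EIH is the mean of three readings, and the pinprick stimulus is fixed. These standardise the tests, but none masks the tester to intensity.

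Nor do the documents show that the supervising physiologist is a spare pair of hands. No section says who does the tests, or that physiologist, researcher and tester are different people. A role split is therefore free only where two people already attend.

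Finally, scripts and analyst masking are commonly left to a fuller protocol or analysis plan, so their absence from an article is not an error. The error is the statement of impossibility. The safeguards are offered as its remedy.

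**Conclusion.** The point holds in a limited form. Section 2.5 states an impossibility that its reason does not support. The tester can be masked at baseline, apart from what carries over from a correct guess at the first session. Postexercise observer bias can be lowered but not removed. Open assessment is disclosed, so the fault lies in the justification and in an inexpensive safeguard passed over.

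The size of the bias is unknown. The 13% and 36% are correct arithmetic on assumed shifts of 0.1 and 0.2 SD, with no true effect, 64 completers and no adjustment. They show that a small systematic shift would matter. They are not an estimate of this trial's error rate, and the alternatives above range from about 6% to 56%. The stated 64 and 80 are unaffected.

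**What to change.** 1. In section 2.5, confine the statement to participants.
2. Where the supervising physiologist and the tester are already different people, let the physiologist run the bicycle, heart rate, perceived exertion and lactate readings. Keep the tester away from the cycling and unaware of session intensity and sequence.
3. In all sessions, script the test instructions and the ice-bath encouragement, hide earlier readings from the tester where feasible, ask participants not to mention effort, and record the tester's guess of the intensity.
4. Give the analyst HIGH and LOW as masked codes until the test choice and models are fixed. This is useful because section 2.9 lets the data decide between parametric and non-parametric tests, and between the regression and the repeated-measures ANOVA.
5. If one person must both run the cycling and test, say so in section 2.5 and list unblinded assessment among the limitations in the Discussion. Items 3 and 4 still apply, as far as they can.

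The cost is a script, masked coding, one extra recorded item and slightly more session organisation. No visit, sample size or exercise procedure changes, and no additional assessor is asked for. The downside is that the tester may still be partly unmasked after HIGH; the recorded guess shows how far.

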### Data collection

2.6

Demographics, including age, sex, education level, duration of chronic NP, physical activity participation level (GPAQ; Cleland et al., 2014) and employment status, will be collected. The outcome assessments consist of questionnaires and central pain processing measurements. Questionnaires will be assessed at the start of each exercise session, and the central pain processing measurements will be performed twice at each session: at baseline; and postexercise.

#### Questionnaires

2.6.1

##### Numerical pain rating scale

Pain intensity will be measured using the numerical pain rating scale (NPRS), which is a valid and reliable tool (Young et al., 2019). The scale is characterized by a line 10 cm in length, with 11 points (0−10) equally spaced on the line, where ‘0’ indicates no pain, and ‘10’ the worst pain imaginable. Participants will be asked to indicate the average NP intensity over the past 24 h and the past 7 days, by placing an ‘X’ on two separate NPRS lines. The NPRS score of average pain intensity will be measured in centimetres, to the nearest tenths.

##### Neck disability index

Disability will be measured using the neck disability index (NDI) questionnaire (Young et al., 2019), which was validated and found to have a high degree of reliability (Vernon & Mior, 1991). The questionnaire consists of 10 items: pain intensity, personal care, lifting, work, headaches, concentration, sleeping, driving, reading and recreation. Each item is rated on a six‐point scale from zero (no disability) to five (complete disability). The numerical responses for each item are summed for a total score ranging between 0 and 50, with a higher score indicating greater disability. If an item (e.g., driving) does not apply to a participant, the item will be omitted from the questionnaire and a proportion score will be calculated accordingly.

##### Pain catastrophizing scale

The pain catastrophizing scale (PCS) is an instrument used to measure catastrophic thinking related to pain and has been used extensively in clinical practice and research (Sullivan et al., 1995). The scale consists of 13 items, measuring catastrophizing thoughts or feelings accompanying the experience of pain. Participants will be asked to rate on a five‐point scale (ranging from 0 =  not at all to 4  =  all the time), based on past painful experiences, and to indicate the degree to which each of the 13 thoughts or feelings were experienced when in pain. The PCS score ranges from 0 to 52, with higher scores indicating a greater pain catastrophizing.

##### Tampa scale of kinesiophobia‐11

The Tampa scale of kinesiophobia‐11 (TSK‐11) is an abbreviated version of the Tampa scale of kinesiophobia (TSK) questionnaire, used to measure fear of movement/(re)injury (Tkachuk & Harris, 2012). The questionnaire uses four points (ranging from strongly disagree to strongly agree) to assess kinesiophobia based on the model of fear avoidance, fear of work‐related activities, fear of movement and fear of re‐injury. The score for TSK‐11 ranges from 11 to 44, with a higher score indicating greater kinesiophobia.

